## Abstract

**Background:**

Berberine is one of the most important examples of a Chinese traditional medicine that has hypoglycemic effects but there have been no randomized controlled trials of the drug in a larger sample. In addition, the use of probiotic biotherapy to maintain an appropriate intestinal flora may represent an effective early intervention for hyperglycemia. Unfortunately, there has been a shortage of relevant research on this possibility at the population level. This study was designed to determine the hypoglycemic effect and safety of both bifidobacteria and berberine administration to newly diagnosed patients with pre-diabetes or diabetes mellitus.

**Methods/design:**

This is a multicenter, double-blind, randomized, and parallel-controlled study that includes a run-in period of 2 weeks and a treatment period of 16 weeks, which will be conducted between June 2015 and October 2018. The 300 randomized patients will be assigned to the following four groups for 16 weeks’ treatment: *Bifidobacterium*, berberine, *Bifidobacterium* combined berberine, and placebo control groups. The primary outcome is the absolute value of fasting plasma glucose compared with baseline after 16 weeks of treatment.

**Discussion:**

This is the first randomized controlled trial to determine the hypoglycemic effect and safety of both bifidobacteria and berberine administration to newly diagnosed patients with pre-diabetes or diabetes mellitus. It may provide support for the use of berberine and bifidobacteria in the treatment of diabetes.

**Trial registration:**

ClinicalTrials.gov, ID: NCT03330184. Retrospectively registered on 18 October 2017.

**Electronic supplementary material:**

The online version of this article (doi:10.1186/s13063-018-2438-5) contains supplementary material, which is available to authorized users.

## Background

According to the latest national epidemiological survey of diabetes, China has prevalence rates of 9.7% and 15.5% for diabetes and pre-diabetes, respectively, among people of over 20 years of age [1], and it has become one of the countries with the largest number of diabetic patients. Oral hypoglycemic drugs have been widely used in China as the recommended first-line treatment, and these can effectively reduce blood glucose [2]. However, adverse reactions or side effects can be associated with their use, albeit benefits that outweigh the risks. For example, metformin can have gastrointestinal effects, sulfonylureas can cause hypoglycemia, and glucagon-like peptide-1 analogs can induce gastrointestinal reactions and antibody formation [3, 4]. Although insulin is relative effective and safe, it may also have risks of hypoglycemia, must be administered by injection and, therefore, its use is less straightforward. Therefore, it is necessary to develop novel effective oral hypoglycemic agents.

Chinese traditional medicine has been used for thousands of years. Diabetes and its treatment were described as early as the Wei and Jin periods (A.D. 220–420), and “Huanglian treats diabetes” was published in the *Renown Physicians’ Extra Records* [5]. With the modernization of traditional Chinese medicine, its use for the treatment of diabetes has attracted greater attention from researchers in recent years. Berberine is one of the most important examples of a traditional Chinese medicine that has hypoglycemic effects [6]. It has been used for the treatment of the complications of diabetes in China for 1500 years [7, 8]. Some studies reported that berberine can improve blood glucose and lipid levels in patients with type 2 diabetes mellitus and dyslipidemia [9–11]. A possible mechanism for its beneficial effects is an increase in the expression and activity of glucose transporter 1, thus increasing the glucose consumption of cells in a non-insulin dependent manner. In addition, it may reversibly inhibit insulin expression, as well as increasing insulin sensitivity at the level of the insulin receptor and activating the insulin signal transduction pathway [12–16].

In addition, because the intestinal tract represents the first organ to be exposed to glucose, and, therefore, has a key role in glucose metabolism, many researchers now believe that the composition of the intestinal flora is important in metabolic diseases such as type 2 diabetes [17–19]. An imbalance in the intestinal flora can result in the presence of deleterious metabolites in the body and cause metabolic endotoxemia, leading to an inflammatory response, the development of insulin resistance, and eventually type 2 diabetes [20]. However, probiotics, such as bifidobacteria, are protective against diabetes because they maintain balance in the intestinal flora [21, 22]. In addition, they may indirectly impact glucose metabolism through effects on intestinal hormones and/or the exocrine pancreas. Previous studies have shown that supplementation with bifidobacteria can improve glucose tolerance and glucose-induced insulin secretion by reducing endotoxemia and proinflammatory cytokine secretion by adipose tissue in high-fat-diet-induced diabetic mice, thus reducing inflammation and ameliorating the metabolic disorders associated with diabetes [22]. Therefore, the use of probiotic biotherapy to maintain an appropriate intestinal flora may represent an effective early intervention for diabetes. Unfortunately, there has been a shortage of relevant research on this possibility at the population level.

Thus, this study was designed to determine the hypoglycemic effect and safety of both bifidobacteria and berberine administration to newly diagnosed patients with pre-diabetes or diabetes mellitus, and their impact on the cardiovascular system, blood lipid metabolism, the intestinal flora, intestinal hormones, body weight, and quality of life.

## Methods/design

This is a multicenter, double-blind, randomized, and parallel-controlled study that includes a run-in period of 2 weeks and a treatment period of 16 weeks, which will be conducted between June 2015 and October 2018.

### Research population and inclusion criteria

The inclusion and exclusion criteria are shown in the Appendix.

### Pharmacologic treatments

The study will include an introductory period of 2 weeks and treatment for 16 weeks (Fig. 1). After the introductory period, the 300 successfully screened subjects will undergo baseline data acquisition and lifestyle guidance and be randomly assigned to the following four groups for 16 weeks’ treatment: *Bifidobacterium*, berberine, combination, and control groups.

**Fig. 1 Fig1:**
[figure not shown]
Inclusion criteria and interventions

The berberine group will receive berberine tablets, 0.5 g, two a day, and *Bifidobacterium* placebo capsules, 0.70 g, two a day, orally. The *Bifidobacterium* group will receive *Bifidobacterium* viable capsules, 0.70 g, two a day, and berberine placebo tablets, 0.5 g, two a day, orally. The combination group will receive *Bifidobacterium* viable capsules, 0.70 g, two a day, and berberine tablets, 0.5 g, two a day, orally. The control group will receive *Bifidobacterium* placebo capsules, 0.70 g, two a day, and berberine placebo tablets, 0.5 g, two a day, orally.

The preparations used will be berberine tablets (Northeast Pharmaceutical Group Shenyang First Pharmaceutical Co., Ltd., Lot No.: 130917), berberine tablet simulant (Northeast Pharmaceutical Group Shenyang First Pharmaceutical Co., Ltd., Lot No.: 20150101), *Bifidobacterium* viable capsules (Livzon Pharmaceutical Group, Lot No.: 20141013), and *Bifidobacterium* viable capsules simulant (Livzon Pharmaceutical Group, Lot No.: 141001).

During the study, researchers will administer other drugs that are not defined within the exclusion criteria and are necessary for the safety and health of the subjects to treat disease or discomfort. All of the drugs administered during the study will be recorded in the corresponding parts of the appropriate Case Report Form (CRF). Here, the specific type of drug (trade name or common name), indications for use, the date, and the dose used will be recorded. In addition, the following drugs will be banned or restricted during the study: any hypoglycemic therapy except for the study drugs, and systemic glucocorticoid (orally or intravenously administered), if used for more than seven consecutive days.

### Lifestyle interventions

Regulation of the diet and exercise of the subjects will be regarded as very important in this study, and discussion and implementation of a diet and exercise plan will be commenced in accordance with researchers’ suggestions from the beginning of the screening period to the end of the trial. A standardized meal suggestion (30 kcal/kg ideal weight/day, based on dietitian recommendations), will be provided, which includes 55% of calories from carbohydrate, 25% from fat, and 20% from protein, with these macronutrients being present in the respective proportions: 1/5, 2/5, and 2/5, and participants will be asked to be strict about their diet and to avoid short-term or high-intensity exercise. Researchers will emphasize the importance of diet and exercise to subjects at each treatment visit.

### Outcomes

The main and secondary outcomes are shown in Table 1.

**Table 1 Tab1:** Primary and secondary outcomes of the trial

Purpose		Measurements
Primary outcome		The absolute value of fasting plasma glucose (FPG) compared with baseline after 16 weeks of treatment
Secondary outcomes	1	The proportion of patients who meet following blood glucose response: (1) HbA1c < 7.0%; (2) HbA1c < 7.0%, without severe hypoglycemia; (3) HbA1c < 7.0%, without diagnosed hypoglycemia; (4) HbA1c < 6.0%; (5) HbA1c < 6.0%, without severe hypoglycemia; (6) HbA1c < 6.0%, without diagnosed hypoglycemia; (7) FPG < 110 mg/dL (6.1 mmol/L); (8) FPG < 130 mg/dL (7.2 mmol/L)
	2	Changes compared with baseline: (1) 2-h postprandial glucose (2-h PPG): (2) glycosylated hemoglobin (HbA1c); (3) 2 h PPG < 140 mg/dL (7.8 mmol/L); (4) 2-h PPG <180 mg/dL (10.0 mmol/L); (5) HbA1c reduced by 0.5%; (6) blood pressure (BP); (7) lipid changes: total cholesterol (Total-C), low-density lipoprotein cholesterol (LDL-C), high-density lipoprotein cholesterol (HDL-C), and triglyceride (TG); (8) Body weight and Body Mass Index (BMI); (9) HOMA Index, insulin early phase and late-phase secretion index; (10) intestinal hormones (GLP-1, glucagon); (11) intestinal flora
Safety purpose		Laboratory data: electrocardiograph (ECG); pulse and blood pressure (BP); weight and physical examination.

*HbA1c* glycosylated hemoglobin

### Participant timeline

The time course for participant registration, intervention, assessment, and follow-up is shown in the Standard Protocol Items: Recommendations for Interventional Trials (SPIRIT) Figure (Fig. 2).

**Fig. 2 Fig2:**
[figure not shown]
Standard Protocol Items: Recommendations for Interventional Trials (SPIRIT) Figure. Specific research plan and implementation steps. Note: Laboratory safety assessment assays were completed by sub-center laboratories, while the validity assessment laboratory assays and the intestinal indices were completed by the central laboratory. *OGTT* oral glucose tolerance test, *BG* blood glucose, *SMBG* self-monitoring of blood glucose, *BMI* Body Mass Index

### Randomization

The stratified blocked randomization method will be used. Stratification will be conducted by each research center to select the appropriate segment length. The statistical software SAS 8.2 PROC PLAN will be used to generate a random code list for 300 subjects to receive specific treatments. All randomized grouping number segments will be sent to the research centers with the corresponding treatment kits. Researchers will then select kits with the same series number for the study according to the visit sequence.

### Blinding and unblinding procedures

Because the two research drugs have different specifications and appearance, double-blind dual simulation will be selected as the method of blinding. The test and placebo drugs will be provided by the coordinating center in identical internal and external packaging.

A two-level blinding design will be used, with the first level being by group (groups A, B, C, and D) according to case number, and the second level by treatment (berberine, *Bifidobacterium*, combination and control). The random code list will be created by a statistical agency, the two-level treatment codes will be sealed separately in duplicate, with a copy being kept by each of the statistical agency and the central coordinator, and the treatment code will be not opened during the study. The study would have been considered invalid if any treatment code disclosure arose from any non-prescribed circumstances and if it affected the objectivity of the data obtained from the study.

A two-phase unblinding method will be adopted. When all of the CRFs have been entered into the database, the first unblinding (identifying groups A, B, C, and D) will be carried out after the blind review, data locking, and statistical analysis plans will be confirmed. The second unblinding will be conducted when the statistical analysis report is completed, to identify subjects in the berberine, *Bifidobacterium*, combination and control groups.

Each coded test drug will have a corresponding emergency letter, describing the subject’s medication, treatment methods, and the organization to which requests for emergency unblinding should be immediately reported. Emergency letters will be sealed and issued to the research center with the corresponding numbers, where they are preserved and not opened unless necessary. In the case of an emergency (for example, a severe adverse reaction), when the type of medication being administered must be known for the effective treatment of the subject, the researcher could access the appropriate letter. In this instance the identity of the opener, the opening date, and the reasons for doing so will be recorded on the CRF. Once unblinded, the subjects will withdraw from the trial, and be treated as expulsion cases. All emergency letters and CRFs will be collected at end of the trial for blind review.

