### Statistical methods

Because no previous studies of treatment with bifidobacteria have been conducted, this represents a pilot study. Sample size was estimated using NCSS PASS 11 (NCSS LLC, Kaysville, UT, USA) software, and it was planned that 300 subjects would be enrolled. The detailed statistical methods are described below.

Superiority hypothesis: in case of occurrence of superiority of either the berberine, *Bifidobacterium* or combination group, the test will be deemed successful, with the bilateral test level for α = 5% (no correction), and for β = 20% (power 80%).

The primary observation indicator in this study was the absolute value of fasting plasma glucose (FPG) compared with baseline after 16 weeks of treatment. The berberine sample size was estimated with reference to the STOP-NIDDM study [4] and Yifei Zhang’s study [11] on the use of berberine to treat type 2 diabetes with hyperlipidemia. In this study, berberine treatment decreased FPG by 1.45 ± 0.85 (standard deviation (SD)) mmol/L, while FPG in the placebo control group decreased by 0.6 ± 1.2 mmol/L. With a difference in FPG between the berberine and placebo groups of 0.85 mmol/L, the estimated pooled variance was 2, and the estimated sample size was 44.

The bifidobacteria sample size was estimated based on a decrease in FPG of 1.2 ± 1.1 mmol/L, and a decrease in FPG in the placebo control group of 0.6 ± 1.0 mmol/L. Assuming that the difference in FPG decrease between the berberine and placebo groups was 0.6 mmol/L, and the estimated pooled variance was 2, the estimated sample size was 88 persons in a single group. Allowing for some expulsions, the final sample size for each group was determined to be 50 for the berberine group, 100 for the *Bifidobacterium* group, 50 for the combination group, and 100 for the placebo control group, giving a total sample size of 300.

The primary analysis population will undergo at least one trial drug treatment and have at least one follow-up record comprising a full analysis set (FAS) and will be analyzed on an intention-to-treat (ITT) basis, including all randomized patients. All support analyses will be based on per-protocol sets (PPSs), and the security endpoint analysis will be based on a safety set (SS). The study will not incorporate a planned mid-point analysis.

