All data will be analyzed using SAS 9.3 (SAS institute Inc, Cary, NC, USA) software using pre-programmed algorithms. Quantitative indices recorded will include the mean ± SD, median, maximum and minimum values; qualitative or grade indices will be recorded using a frequency distribution table. Two-sided tests will be used in all cases, and *P* ≤ 0.05 will be considered to be statistically significant. Fisher’s exact probability test will be used to compare the expulsion rates between the groups.

Validity analysis will be based on the FAS, using a covariance analysis model, with the main and secondary efficacy index baseline values being the covariates in the model, and the central effect serving as the fixed-effect term. The least squares estimates will be used to calculate the corrected mean and the 95% confidence intervals for changes in each group, and the 95% confidence interval of the Dunnett corrected mean difference between the test and placebo groups will be used to fit a covariance analysis model with central and group interactions to test the consistency among study centers. The applicability of this covariance analysis model will be investigated at the level of α = 0.10. Unless otherwise specified, the method of Carrying Forward (last observation carried forward, LOCF) will be used for sensitivity analysis of each validity analysis.

Security analysis will be based on a SS. Safety endpoints will be analyzed and adverse events aggregated. The continuous variables or frequency counts and percentage in safety and tolerability endpoints will be analyzed using descriptive statistics. The relative indices for hypoglycemic events and changes in weight will be compared between groups according to general principles.

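### An emergency code break takes the subject out of the trial, so the week-16 FPG is lost after an event that treatment may cause, contrary to the all-randomised ITT analysis

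*Protocol article*

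**What the plan says.** The section on blinding and unblinding provides sealed emergency letters, to be opened only when effective treatment requires knowledge of the medication: "In the case of an emergency (for example, a severe adverse reaction"). The opener, date and reason go on the case report form. The consequence is then fixed: "Once unblinded, the subjects will withdraw from the trial, and be treated as expulsion cases".

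The Statistical methods section defines the primary population: "The primary analysis population will undergo at least one trial drug treatment and have at least one follow-up record comprising a full analysis set (FAS"). The same sentence adds that it "will be analyzed on an intention-to-treat (ITT) basis, including all randomized patients". Supporting analyses use per-protocol sets and safety uses a safety set. Last observation carried forward is named for sensitivity analysis of the efficacy results.

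Table 1 gives the primary outcome: "The absolute value of fasting plasma glucose (FPG) compared with baseline after 16 weeks of treatment".

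The article does not define *expulsion*. The term appears in two other places: the sample-size allowance ("Allowing for some expulsions, the final sample size for each group was determined to be 50 for the berberine group") and a between-group comparison ("Fisher’s exact probability test will be used to compare the expulsion rates between the groups").

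**The concern.** The trigger for opening a letter is a post-randomisation event, and on the plan's own example it can be a reaction to the study drug. Tying withdrawal from the trial to that event makes absence of the endpoint depend on what happened under treatment. An ITT analysis is meant to prevent this kind of selection.

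The endpoint is a laboratory glucose value, so knowing the allocation gives little reason to stop measuring it. The rule therefore gives up information that the primary analysis needs and gains little for the blind. It is also a stated rule and not a detail left to a fuller document, so the brevity of an article does not explain it.

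**Working it through.** **1. How the plan treats expulsions in its sample size.** Inputs from Statistical methods: differences of 0.85 and 0.6 mmol/L, variance 2, two-sided 5% level, 80% power. The formula is n per group = 2 × variance × (z for 97.5% + z for 80%)² / difference², where (1.960 + 0.842)² is about 7.85.

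- Berberine: 2 × 2 × 7.85 / 0.85² = 31.4 / 0.7225 = 43.5, rounded up to 44. This matches the article.
- *Bifidobacterium*: 31.4 / 0.6² = 31.4 / 0.36 = 87.2, rounded up to 88. This matches the article.
- Allowance: 1 − 44/50 = 0.12 and 1 − 88/100 = 0.12. Conversely, 44/0.88 = 50 and 88/0.88 = 100.

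The article does not state 12%; it is back-calculated, and the final sizes could simply be round numbers. Either way, the numbers were raised to make up for expulsions. This suggests that the planners expected these subjects to contribute no endpoint.

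**2. What happens to a code-broken subject.**

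- The blinding section withdraws the subject from the trial. If this happens before week 16, there is no week-16 FPG.
- Statistical methods says that all randomised patients are analysed. By the definition in that section, a subject with one dose and one follow-up record belongs to the full analysis set.
- The subject may therefore be in the analysis set by definition, yet have no endpoint because of the withdrawal rule. The article does not say whether expulsion status overrides membership of the set.
- Carrying the last value forward is assigned to sensitivity analysis, so it is not the stated means of filling the gap in the primary analysis.

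**3. Size, under assumption.** If a share f of an arm is unmeasured and its mean FPG change differs by g from the rest, the mean of the measured subjects differs from the full-arm mean by f × g. The number of code breaks is not given, so f and g are assumptions.

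- One of 50 berberine subjects, with the placebo fall of 0.6 instead of 1.45 mmol/L: f = 1/50 = 0.02, g = 1.45 − 0.6 = 0.85, shift = 0.02 × 0.85 = 0.017 mmol/L. Relative to the planned 0.85 this is 2%.
- f from 1% to 5% and g from 0.5 to 1.45 mmol/L: from 0.01 × 0.5 = 0.005 to 0.05 × 1.45 = 0.0725 mmol/L.

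The sign depends on which arm loses the subject and on whether that subject's glucose fell more or less than the others'.

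**The case against.** The strongest reply is that this is ordinary dropout under another name. Letters stay closed unless necessary, so few subjects will be affected. A missing week-16 value is a missing-data problem and does not in itself exclude anyone from ITT. Naming last observation carried forward shows that the plan expects incomplete follow-up within the full analysis set. Much of this stands, and it limits the size of the point. It does not remove it: most dropout cannot be prevented, whereas this loss is imposed by the protocol.

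A reader might infer four stronger things that the document does not support:

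- *Data already collected are thrown away.* Nothing says that earlier values are deleted or that expulsion cases leave the full analysis set. Withdrawal stops future collection only.
- *Adverse-event follow-up stops.* The article does not say so. Safety has its own analysis set, no text removes expulsion cases from it, and follow-up of an ongoing event after withdrawal is commonly left to the full protocol.
- *The bias favours the active arms.* The trigger is any emergency in which the medication must be known, and a severe reaction is only an example. Emergencies can occur in any arm. Losing poorly controlled placebo subjects, or strong responders on active drug, would work the other way.
- *The effect could be overstated by about 0.10 mmol/L.* This needs 6 of 50 berberine subjects lost (0.12 × 0.85 = 0.102). That is the whole apparent allowance for expulsions of every kind, spent on code breaks in one arm with none in placebo.

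A separate tension lies within Statistical methods itself, where a population requiring a dose and a follow-up record is said to include everyone randomised. It is not the point made here.

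**Conclusion.** The point holds in limited form. The blinding section ends collection of the primary endpoint after an event that may be related to treatment. This conflicts with the all-randomised analysis in Statistical methods, and the article leaves the analysis status of expulsion cases open.

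The effect on the primary estimate is probably small: about 0.017 mmol/L for one berberine subject, assuming the placebo response in that subject and no code breaks elsewhere. The frequency of code breaks and the direction of bias are not known from the document. This is a cheap improvement, not a threat to the trial's validity.

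**What to change.** Reconcile the blinding section with Statistical methods, for example with this text:

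*Opening an emergency letter does not by itself end a subject's scheduled outcome and safety assessments. Subjects who continue to consent are measured at week 16. They remain in the full analysis set, where they meet its definition, and in the safety set, as randomised. The code break is recorded and excludes them only from the per-protocol set.*

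Define *expulsion* to match, so that the sample-size allowance, the Fisher comparison and the analysis sets all use the term in one sense. Any rule on study drug after a code break lies outside this change and should be left as it is.

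The cost is a short amendment and a few extra scheduled visits for what are probably few subjects. The article reports that recruitment was still open, so the change could apply to subjects yet to be treated.
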